#### Secondary outcomes

The secondary outcomes are as follows: *Nursing practice*: Nurses’ adherence to CPGs measured by proportions of documented VS (complete set), repeated VS within 30 min of obtaining an abnormal VS and documented nursing scope of practice interventions in response to abnormal vital signs; proportions of activated urgent clinical reviews and MET calls in patients fulfilling the criteria. *Clinical:* Rates of cardio-respiratory arrests, unplanned admissions to ICU, unexpected hospital mortality and mean HLOS. *Costs:* Mean additional cost of implementing the intervention and mean/median total hospital cost and HLOS for patients. *Process evaluation*: measurement of the fidelity of the facilitation intervention, contextual influences and impact on ward processes and practice.

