### Setting

Four hospitals in Victoria, Australia, will be the setting for this study. All are acute, major metropolitan teaching hospitals that have more than 400 beds, employ over 1300 nurses and cover both acute and specialist services. Sponsorship for the study was sought from the Executive Directors of Nursing and Chief Executive Officers of each hospital prior to the funding application. Within each hospital, eight to ten wards will be randomly allocated to either intervention or control groups; the intervention will be delivered at ward level. Each ward is considered a cluster for the purpose of analysis. Wards will be eligible for inclusion if they contain 18 or more beds and they receive support from the hospital’s MET. Critical care, emergency, paediatrics, maternity, peri-operative and psychiatric areas will be excluded because they use an alternative response system for patient deterioration.

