### Sample/participants

All staff working within study wards and whose role is direct care delivery will be involved in the study. Each ward has a permanent staff, reducing the likelihood of contamination from staff movement. Nurse managers (NM) will recruit staff to participate in focus groups or individual interviews for the process evaluation; the RA will obtain consent. Medical records of patients from participating wards will be audited over three randomly selected 24-h periods during 1 week at three time points (baseline, immediately post-intervention and 6 months post-intervention) to identify all ward patients in a 24-h period who have abnormal VS. These cohorts of patients will be followed up for the duration of their hospital stay and analysed according to ward (intervention or control), irrespective of subsequent ward transfers that may occur using the principles of intention-to-treat (ITT) analysis.

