### Randomisation

Random 1:1 block randomisation of wards within hospitals to intervention or control groups will be undertaken. A central randomisation service independent of the study will be used with concealment until the intervention is assigned. Assessment days will be randomly selected.

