### Data analysis

Quantitative methods will be used to analyse patient, health services utilization and economic outcomes. Main and secondary outcome analysis will be based on all randomised wards and selected participants (intention-to-treat analysis). To account for within-patient correlation, due to multiple measurements from the same patient during assessment days, we will implement generalized estimating equation (GEE) models with binary outcome and logit link for all rate outcome comparisons [23]. The Cochran-Mantel-Haenszel (CMH) test will be used to compare proportions. Clustering effects for wards will be evaluated by calculating intraclass correlation coefficients and, if necessary, a fixed effect nominal factor will be included in GEEs to account for ward impact. A series of exploratory analyses will be conducted on subgroups and the impact of covariates on estimates of the effect of the intervention. A nonparametric median test will be used for HLOS comparison. In supportive analysis, HLOS will be considered as time to event data. Survival rates will be calculated and illustrated by the Kaplan–Meier method and further analysed by the log-rank test for univariate analysis (stratified by wards). Variables that reveal prognostic or effect modifying potential on the outcome as suggested by univariate analysis will subsequently be evaluated by the proportional Cox regression for multivariate analysis. Hazard ratios with the corresponding 95% confidence intervals will be reported. A *p* value of <0.05 is considered statistically significant. Data will be analysed using Stata version 14 or later [24].

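### The supportive log-rank test of HLOS is stratified by the randomised unit, so its arm comparison cannot be computed, and the main HLOS median test states no allowance for ward clustering

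*Protocol article*

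**What the plan says.** The Randomisation section states: "Random 1:1 block randomisation of wards within hospitals to intervention or control groups will be undertaken". Setting adds that "Each ward is considered a cluster for the purpose of analysis" and that "the intervention will be delivered at ward level". Under Sample/participants, audited patients are "analysed according to ward (intervention or control), irrespective of subsequent ward transfers that may occur". Together these place each ward, and every patient counted under it, in a single arm.

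Data analysis gives two HLOS analyses for the audited patients. The main one reads: "A nonparametric median test will be used for HLOS comparison". The supportive one treats HLOS as time to event, with Kaplan–Meier curves, and is "further analysed by the log-rank test for univariate analysis (stratified by wards"). Variables that look prognostic or effect-modifying then go into a Cox model. The only remedy for ward effects named in that section is a fixed ward factor in the GEE models, which are specified for binary outcomes.

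The secondary hypotheses state the HLOS hypothesis as a comparison between arms: a shorter stay for patients in FLIP wards.

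**The concern.** A stratified log-rank test compares groups inside each stratum and then adds up the comparisons. When the stratum is the unit that was randomised, there is nothing inside any stratum to compare. The article names the stratification factor, so this is a stated rule that does not fit the design, not a detail left to a later document.

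The main HLOS test has the opposite problem: as described, it treats patients as independent although whole wards were allocated. If both analyses stay as written, one planned arm test for the audited cohort gives no result, and the other overstates the evidence to the extent that patients in the same ward have similar stays. The analyst would then have to choose a replacement for the log-rank test after data collection.

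**Working it through.** **Inputs.** The ward is the unit of randomisation, blocked within hospital (Randomisation). There are four hospitals with eight to ten wards each, so 32 to 40 wards (Setting). Patients are assigned to arm by ward, whatever their later transfers (Sample/participants). The log-rank stratum is the ward (Data analysis).

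**Log-rank test, algebra.** At each event time in a stratum, let n be the number at risk, n1 the number at risk in the intervention arm, and d the number of events. Then

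- E = d × n1/n
- V = d × (n1/n) × (1 − n1/n) × (n − d)/(n − 1)
- statistic = [Σ(O − E)]² / ΣV, summed over event times and strata.

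In an intervention ward n1/n = 1, so E = d = O and V = 0. In a control ward n1/n = 0, so E = O = 0 and V = 0. Every stratum contributes nothing to the numerator or the denominator, and the statistic is 0/0.

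**Log-rank test, numerical check.** Ward-randomised stays were simulated with 15 patients per ward and a strong HLOS effect (both assumptions, for illustration only).

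| Wards | Arm, stratified by ward | Arm, stratified by hospital | Patient covariate, stratified by ward |
|---|---|---|---|
| 32 | O − E = 0, V = 0 | O − E = 57.06, V = 96.2, χ² = 33.8 | V = 82.9 |
| 36 | O − E = 0, V = 0 | O − E = 64.25, V = 105.9, χ² = 39.0 | V = 88.7 |
| 40 | O − E = 0, V = 0 | O − E = 74.13, V = 117.4, χ² = 46.8 | V = 109.0 |

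On the 40-ward data a standard survival routine, asked for the ward-stratified arm test, stopped with a singular-matrix error. The hospital-stratified χ² values show only that the test can be computed. They still ignore ward clustering and should not be read as valid significance levels. The last column shows that ward stratification does no such harm to covariates that vary within a ward.

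**Where the plan's design effect belongs.** The Sample size section asks for 270 abnormal vital signs per arm and time point. Take 50% against 70%, two-sided 1% and 90% power. The pooled two-proportion formula gives [2.576 × √0.48 + 1.282 × √0.46]² / 0.20² ≈ 176.1, that is 177, and 177 × 1.5 = 265.5, close to 270. The 1.5 thus belongs to the adherence calculation, and the section says it covers correlation within patients as well as within wards. It is not an HLOS figure.

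**Median test.** If ward clustering multiplies the variance of the arm contrast by k and the test ignores it, the true size of a nominal 5% test is 2 × [1 − Φ(1.96/√k)].

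- k = 1.1: 1.96/1.049 = 1.869, size 6.2%
- k = 1.5: 1.96/1.225 = 1.600, size 11.0%

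The article gives no HLOS intraclass correlation, so this range of k is an assumption.

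**The case against.** The strongest reply is that the affected test is minor. It is a supportive analysis of a secondary outcome, described as univariate and used to screen variables for the Cox model, where stratifying by ward is legitimate for patient-level factors. The Cox model is not said to be ward-stratified, so an arm hazard ratio can still be estimated, and Kaplan–Meier curves by arm are unaffected. All of this stands and limits the reach of the point. It does not rescue the arm test.

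The phrase could also be loose wording for ward group, since Sample/participants uses ward in that sense when it classifies patients. That is possible, but the text names wards as strata. If groups were meant, the sentence still needs correcting, and clustering would then be unaddressed. Pooling baseline with later periods would leave some within-ward information, but only as a before–after contrast, which the article does not describe.

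A reader might infer several stronger things that the article does not support:

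- **No valid test of the HLOS hypothesis, and a damaged economic claim.** The Cost analysis section plans a difference-in-difference comparison of mean HLOS between intervention and control wards, on all complete admissions. That does not depend on the log-rank test.
- **An 11% error rate as the plan's own figure.** The 1.5 behind it was set for vital-sign adherence and includes within-patient correlation.
- **A mean is required in place of the median.** Secondary outcomes does list "unplanned admissions to ICU, unexpected hospital mortality and mean HLOS", but Sample size powers HLOS on a median difference (12 against 10.4 days). Keeping the median is defensible.
- **Survival-time bias because patients enter on audit days.** This presumes time counted from admission without delayed entry. The article gives no time origin, and that detail may sit in the full plan.

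**Conclusion.** The point holds in a limited form. The ward-stratified log-rank test of the intervention effect on HLOS is 0/0 by construction. This rests only on each ward being in one arm and on the sentence meaning what it says.

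Separately, the median test has no stated adjustment for wards, so positive correlation between patients of the same ward makes its p value too small. The direction is clear but the amount is not: about 6% to 11% true size under an assumed inflation of 1.1 to 1.5. The primary outcome, the Cox model and the difference-in-difference analysis are untouched by the stratification error. The correction should be made, but it does not threaten the trial's main conclusion.

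**What to change.** In Data analysis:

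1. Stratify the log-rank test of the arms by hospital, the randomisation stratum, instead of by ward.
2. Allow for ward clustering in the time-to-event analysis, including the Cox model, by a ward-clustered robust variance or a shared ward frailty.
3. Replace the plain median test by a version that respects wards, for example median regression with ward-clustered standard errors or a permutation test that reallocates whole wards within hospital. The median can stay as the target.

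The cost is slightly wider intervals and a little extra analysis work. No new data are needed.

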### Instruments

The electronic Case Report Form (eCRF) was adapted from our previous research [6, 7] to collect data relating to (1) documented vital signs (respiratory rate, heart rate, temperature, blood pressure, conscious state and oxygen saturation), CRC and MET activations; (2) patient outcomes, including unplanned ICU admissions, cardio-respiratory arrests, limitations of medical treatment orders, LOS and inpatient mortality; and (3) nursing interventions and referrals in response to abnormal vital signs and escalation as per hospital policy.

Electronic Activity and Communication Log (eACL) data will be collected at the time of activity and throughout the duration of the intervention. Data captured will include methods and techniques outlined in the Facilitator Manuals, enablers and barriers, and measures of impact.

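### The covariate screen for the supportive Cox analysis of hospital stay is not limited to pre-intervention variables, so it can admit mediators and bias the FLIP hazard ratio

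*Protocol article*

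**What the plan says.** All of this is in the protocol article.

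- **Main HLOS analysis (Data analysis):** "A nonparametric median test will be used for HLOS comparison". No covariates are involved.
- **Supportive HLOS analysis (same section):** "In supportive analysis, HLOS will be considered as time to event data". After Kaplan–Meier curves and log-rank tests, the candidates taken into a multivariable Cox model are "Variables that reveal prognostic or effect modifying potential on the outcome as suggested by univariate analysis". Hazard ratios with 95% confidence intervals are to be reported.
- **Rate outcomes, including the primary (same section):** "generalized estimating equation (GEE) models with binary outcome and logit link for all rate outcome comparisons", with a ward factor if needed. No univariate screen is attached to these models.
- **Other covariate work (same section):** "A series of exploratory analyses will be conducted on subgroups and the impact of covariates on estimates of the effect of the intervention". No covariates are named and no selection rule is given.
- **What is recorded (Instruments):** vital signs with clinical review and MET activations; "unplanned ICU admissions, cardio-respiratory arrests, limitations of medical treatment orders, LOS and inpatient mortality"; and nursing interventions, referrals and escalation. Table 1 adds repeat vital signs within 30 minutes. Neither place lists demographic or admission characteristics.
- **What FLIP should change (Secondary hypotheses):** more complete and repeated vital signs, more nursing interventions, more reviews and MET calls, fewer arrests and unplanned ICU admissions, lower unexpected mortality and shorter stay. Escalation is the primary outcome.

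**The concern.** A covariate in a model for a randomised comparison should be fixed before the intervention can affect it. The rule here asks only whether a variable predicts stay. A variable that FLIP changes, and that in turn changes stay, can pass that test. Once it is in the model, the FLIP coefficient no longer measures the total effect of FLIP but only the part not passing through that variable. If the variable also shares unmeasured causes with stay, such as severity, conditioning on it adds a further bias.

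The mention of effect-modifying potential implies that allocation is in this Cox model, because a variable can modify an effect only relative to the intervention. HLOS is a secondary outcome, and the economic hypothesis relies on a shorter stay. In the Data analysis section the hazard ratio is also the only HLOS effect measure with a stated confidence interval. A value near 1 after adjusting for escalation could be misread as FLIP having no effect on stay.

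**Working it through.** **1. The plan's own figure.** The check uses 50% v 70% escalation, so I first confirmed that the 20% improvement under Sample size is absolute. Two-sided alpha 1%, power 90%, mean proportion 0.60:

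n = [2.576 × √(2 × 0.60 × 0.40) + 1.282 × √(0.50 × 0.50 + 0.70 × 0.30)]² / 0.20² = 176.1, so 177 per arm. Times the design effect of 1.5 this is 266, against 270 stated. A relative reading (50% v 60%) gives 1103. So 50% v 70% is the planning assumption. The sample size is not affected by this point.

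**2. Which recorded variables lie on FLIP's path.**

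| Recorded variable | Hypothesised to change under FLIP? |
|---|---|
| Repeat vital signs, nursing interventions | Yes |
| Clinical review and MET activation, escalation | Yes |
| Unplanned ICU admission, arrest | Yes |
| Treatment-limitation orders | Not stated |
| The abnormal vital sign values that define the cohort | Not stated |

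**3. Effect of adjusting for one mediator, closed form.** Suppose FLIP acts only through escalation and escalation multiplies the discharge hazard by h (assumed; not in the article). At the start of stay, the FLIP hazard ratio without adjustment for escalation is

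HR = [1 + 0.70(h − 1)] / [1 + 0.50(h − 1)].

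- h = 1.25: 1.175 / 1.125 = 1.04
- h = 1.5: 1.35 / 1.25 = 1.08
- h = 2.0: 1.70 / 1.50 = 1.13

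Given escalation status, the FLIP hazard ratio is 1.00 in every case.

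**4. The same by simulation.** 1000 patients, no ward clustering, 100 replicates per row. The screen is a univariate p < 0.05 for escalation.

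| Assumed h | Direct FLIP effect | FLIP HR, baseline covariate only | FLIP HR, adjusted for escalation | Escalation passes screen |
|---|---|---|---|---|
| 1.25 | none | 1.05 | 0.99 | 89% |
| 1.5 | none | 1.08 | 1.00 | 100% |
| 2.0 | none | 1.15 | 1.01 | 100% |
| 1.5 | HR 1.1 | 1.19 | 1.09 | 100% |

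The last row agrees with 1.10 × 1.08 = 1.19: only the mediated part is lost.

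**5. Direction when severity confounds.** Let unmeasured severity lower the discharge log-hazard by 0.7 per SD and raise the odds of escalation, with h = 1.5 and no direct effect. At a severity log-odds ratio of 1.0 for escalation, adjustment moved the FLIP HR from 1.06 up to 1.09; at 1.5, from 1.06 up to 1.12. Milder settings gave attenuation. The direction is therefore not fixed.

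**6. ICU admission.** At the planning rates (1.2% v 0.9%), and assuming ICU admission cuts the discharge hazard to one third, adding it moved the FLIP HR from 1.165 to 1.163. A variable this rare has little leverage; escalation matters far more.

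**7. Do the plan's HLOS figures settle the size?** No. If stay were exponential, medians of 12 v 10.4 days would give HR = 12 / 10.4 = 1.154. Setting the formula in step 3 equal to 1.154 gives h − 1 = 0.154 / (0.70 − 0.577) = 1.25, so h is about 2.25. Full mediation at that size needs escalation to more than double the discharge hazard, which nothing in the article establishes.

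**The case against.** A reader might infer that the trial's adjusted effect in general is compromised. The article does not support that. The rule sits inside a supportive analysis of one secondary outcome; the GEE and Cochran-Mantel-Haenszel analyses carry no such screen, and the median test has no covariates.

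A reader might also infer that the recorded items are the covariates, or that all of them are consequences of FLIP. The Instruments section says what is collected, not what will enter a model. The same items are collected at baseline, before FLIP. Treatment-limitation orders and the presenting abnormal values are not hypothesised FLIP effects. So the admission of mediators is something the rule permits, not something the article announces. Nor does the rule extend to the exploratory work on "the impact of covariates on estimates of the effect of the intervention", for which no selection rule is given.

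Finally, a covariate list may sit in a full protocol or analysis plan that is not shown. Leaving out a list would be no fault in an article. But this article prints a selection rule, and a rule driven by univariate results is not the same as a list fixed in advance. That part of the concern stands.

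**Conclusion.** The point holds in a narrow form. As stated, the covariate rule for the supportive HLOS Cox model can admit variables on FLIP's causal path and so bias that model's FLIP hazard ratio. Where FLIP acts through escalation and severity does not confound, the bias is towards 1: 1.08 to 1.00 at an assumed escalation HR of 1.5, and only the mediated part is lost if there is also a direct effect. Where sicker patients are escalated much more often and stay longer, the bias can be away from 1.

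These sizes rest on assumed escalation and severity effects, exponential stay and no ward clustering; only the 50% v 70% comes from the article. They also require that a mediator is selected and that allocation is in the same model. The primary outcome, the other rate outcomes and the main HLOS comparison are not affected.

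**What to change.** Replace the univariate screen for the Cox treatment-effect model with a short list of covariates specified in advance and fixed before FLIP could act: for example hospital, the ward's baseline-period value, and patient characteristics at admission. That such patient characteristics can be obtained is an assumption, since the article does not list them.

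State that escalation, clinical review and MET activation, repeat vital signs, nursing interventions, ICU admission and arrest do not enter that model. Report any model that contains them separately, labelled as exploratory or as mediation analysis.

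The cost is a sentence or two in the analysis section, with no change to sample size. Trial status says data collection is under way, so the change should be made before any comparison by arm. The one small loss is that the adjusted model can no longer add strong predictors found in the data.

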#### Cost analysis

Analysis of the costs of hospitalisation will be determined at the patient level over the 6-month period for intervention and control wards. All patients admitted to the study wards during the 6-month study period will be included in the analysis of mean total cost, HLOS and ICU LOS for intervention and control wards in each hospital. Only complete admissions will be included (patients admitted to a study ward and discharged from the hospital within the study period); and patients will be analysed based on their admission ward. Mean costs and HLOS for each patient in each ward will be compared to costs and HLOS for patients admitted to the same wards in the 6 months prior to the study period. Difference in difference analyses will be undertaken to compare the mean cost and HLOS difference between pre-intervention and intervention periods, and between intervention and control wards across hospitals. Costs will be attributed to the FLIP intervention based on the additional costs of the implementation process (staff time) over standard in-hospital CPG training.

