### Secondary hypotheses

*Nursing practice outcomes*: Patients in wards receiving the FLIP will have increased documented VS (complete sets), repeated VS within 30 min of obtaining an abnormal VS, documented nursing scope of practice interventions in response to abnormal vital signs, increased activations for urgent clinical reviews and MET calls in patients fulfilling the criteria. *Clinical Outcomes*: Patients in wards receiving the FLIP will have fewer cardio-respiratory arrests, less unplanned intensive care unit (ICU) admissions, lower unexpected hospital mortality rates and reduced hospital length of stay (HLOS). *Health Economic Outcome*: The cost of implementing the FLIP will be offset by savings from shorter HLOS and reduced ICU admissions. FLIP will represent a cost-effective use of resources.

The study is designed to adhere to the Good Clinical Practice (GCP) Guidelines for national ethics standards and is consistent with the C-RCT CONSORT statement [19] and the CHEERS statement [20], ensuring it meets international ethical and scientific quality standards for reporting clinical trials that include an economic evaluation (see Fig. 1).

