### Assessments

#### Aims 1 and 2

Outcome data collection will occur across three time points: at baseline prior to implementation, immediately following completion of the intervention (6 months) and 6 months post-intervention (12 months). At each time point, the medical records of all inpatients admitted to study wards will be reviewed by a RA (blinded to group allocation) to determine if abnormal VS were present, and if so, the rates of escalation as per hospital policy, HLOS, unplanned ICU admissions and unexpected inpatient mortality. Data collection days will be randomly selected. RAs will be trained in data entry. Prior to RAs collecting data independently, inter-rater reliability will be evaluated by the project manager who is a registered nurse with specialist intensive care qualifications. Independent data extraction will be conducted until >95% agreement is obtained. The secure data entry system will not allow invalid values; data backup measures will be installed. Costs attributed to FLIP and training will be calculated.

#### Aim 3

Facilitators will complete electronic activity logs; ward communication and policy changes will be collected by RAs electronically. To capture the experience of FLIPs and key stakeholders regarding the intervention and CPG implementation, semi-structured individual and focus group interviews and field observations will be conducted at critical points in the project—before, during and after the intervention. Interviews will be audio-recorded and transcribed verbatim.

All assessments are outlined in Table 1.

**Table 1 Tab1:** Data collection

Aim	Variable/Measure	Instrument	Outcomes	Data collection point
1	Adherence to CPG	eCRF	CPG element compliance: completed VS documentation; repeated VS within 30 min; interventions within scope of practice; CRC and MET activations; escalation as per hospital policy.	Baseline^a^, 6 and 12 months^b^
2	Patient outcomes	eCRF; Hospital clinical databases	Unplanned ICU admissions, cardio-respiratory arrests, limitations of medical treatment orders, HLOS and inpatient mortality.	Baseline^a^, 6 and 12 months^b^
2	Hospital costs	CRF; Hospital clinical costing databases.	Unplanned ICU admissions, HLOS and inpatient mortality; total cost of hospital episode.	Hospital episode^b^
2	Intervention costs	CRF; Staffing salaries	FLIP cost; training frequency	Continuous
3	FLIP dose	eACL	Contact and content of contact.	Continuous

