3	Enablers/barriers	eACL/ Ward Communication Books, RISKMAN incidents, Focus groups.	Issues arising; Critical incident analysis.	Continuous
3	Ward Impact	Ward Communication Books, policies and procedures, interviews, field observations.	Frequency and content.	Continuous
3	Facilitator Impact	Interviews with all FLIPS	Perceptions and content.	6 months^b^

^a^Prior to commencement of intervention (baseline)

^b^On completion of intervention (6 and 12 months post-baseline data collection)

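### Hospital costs are compared only for the 6 months of FLIP delivery, while consequences are assessed at 6 and 12 months, so the cost-offset test leaves out any savings after month 6

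*Protocol article*

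**What the plan says.** All references are to the protocol article.

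- **Cost window.** Under Cost analysis: "Analysis of the costs of hospitalisation will be determined at the patient level over the 6-month period for intervention and control wards". The comparator is patients "admitted to the same wards in the 6 months prior to the study period".
- **Which 6 months.** The same section says that the difference-in-difference analysis will "compare the mean cost and HLOS difference between pre-intervention and intervention periods", and between arms. The after-period is therefore the delivery period, which the Abstract and the Intervention group section put at 6 months. Only admissions that both begin and end inside the window count.
- **FLIP cost.** It is the extra staff time that implementation needs beyond usual guideline training. Nothing spreads it over a longer benefit period.
- **Hypothesis.** Under Secondary hypotheses: "The cost of implementing the FLIP will be offset by savings from shorter HLOS and reduced ICU admissions". No time horizon is named.
- **Timing of consequences.** Under Assessments, outcomes are collected at baseline, then "immediately following completion of the intervention (6 months) and 6 months post-intervention (12 months" after baseline. The Sample size section bases the power statements for ICU admission and HLOS on the two post-intervention points combined.
- **Table 1.** The hospital-cost row gives the hospital episode as its collection point, with footnote b: "On completion of intervention (6 and 12 months post-baseline data collection".

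**The concern.** The offset hypothesis sets one sum of money against another. The plan takes the spending in full but takes the savings only from the months in which facilitators are at work. The trial looks for its HLOS and ICU effects at the end of those months and again half a year later. The two quantities meant to generate the savings are thus tested after delivery but valued only during it.

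Two things are at stake. First, if the effect outlasts facilitation, the trial could conclude that FLIP does not pay for itself because the later savings were never counted. Second, the cost consequence analysis would place effects from months 6 and 12 beside a cost difference from months 0-6, and a reader could take them as describing the same period.

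**Working it through.** The plan states no FLIP cost, no cost per bed-day and no time course of effect, so there is no cost figure to reproduce and a corrected net cost cannot be computed. Two checks are possible.

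**1. The periods side by side**

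| Item | Period covered | Section |
|---|---|---|
| Hospital cost, HLOS and ICU LOS in the economic comparison | months 0-6 against the 6 months before | Cost analysis |
| FLIP cost | all additional implementation staff time | Cost analysis |
| Clinical outcomes, including HLOS and ICU admission | baseline, month 6, month 12 | Assessments; Sample size |
| Hospital-cost row | hospital episode, footnote b (6 and 12 months) | Table 1 |

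No rule in the Cost analysis section brings in costs from months 6-12.

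**2. Share of a 12-month saving that the window can see**

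Let E(t) be the monthly saving at month t as a fraction of its maximum, with admissions per month taken as constant (an assumption). Then

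share counted = (area under E from 0 to 6) / (area under E from 0 to 12).

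Every curve below is assumed.

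| Assumed course of effect | Months 0-6 | Months 6-12 | Share counted |
|---|---|---|---|
| Linear build-up to month 6, then held | 3.0 | 6.0 | 3/9 = 33% |
| Build-up to month 6, half lost by month 12 | 3.0 | 4.5 | 3/7.5 = 40% |
| Build-up over 3 months, then held | 4.5 | 6.0 | 4.5/10.5 = 43% |
| Constant from day 1 to month 12 | 6.0 | 6.0 | 6/12 = 50% |
| Build-up to month 6, fading to zero at month 12 | 3.0 | 3.0 | 3/6 = 50% |
| Constant from day 1, ending at month 6 | 6.0 | 0.0 | 6/6 = 100% |

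The constant-effect row shows that the omission does not depend on a gradual build-up.

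**What this means for the offset test.** Let C be total FLIP cost and S the 12-month saving. The plan compares (share x S) with C. Suppose FLIP exactly breaks even over 12 months, so S = C. The plan would then show savings equal to share x C: half of the cost under a constant effect, one third under build-up then held, and the full cost if the effect stops with facilitation.

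**The case against.** **The horizon is a design choice.** The hypothesis names no horizon, and costing a 6-month programme over its 6 months is coherent. If the effect lasts, it is also conservative against FLIP. A 12-month horizon moves the cut-off rather than removing it. This stands, and it is why explicitly limiting the claim to the delivery period is an acceptable alternative. It does not explain why costs stop at month 6 when the trial's own last assessment is at month 12.

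**Build-up is not in the text.** A reader might infer that the window holds only a ramp-up phase, so that only one third to one half of the savings is counted. The documents do not support this. Hospital-facilitator support is a steady 5 h per week, barriers are reviewed before the start, and an effect that is strongest while facilitators are present fits equally well.

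**Persistence is under test.** The 20% improvement in the Sample size section is a detectable difference in escalation adherence at both post-intervention points. It is not a forecast that HLOS or ICU savings will last. This stands: the direction of any bias is conditional.

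**Table 1 is ambiguous.** Footnote b also marks the facilitator-impact row, which is collected at 6 months only, so it may be a loose note. If it does mean both points, Table 1 already foresees later costs. In either case the table and the Cost analysis section need reconciling.

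**Later HLOS and ICU data exist.** They do, but in audited cohorts of patients with abnormal vital signs found on three sampled days per time point. The economic comparison uses every complete admission to the study wards, so the audits do not replace it.

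**Season and timing of spending.** A reader might also infer that two consecutive half-years confound the result by season, or that all spending falls inside the window. Concurrent control wards randomised within the same hospitals remove shared seasonal change, leaving chance imbalance. The documents do not date the training relative to month 0. Neither inference is part of this point.

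**Conclusion.** The mismatch is real and is a stated rule: the section fixes the window, the comparator and the contrast, so it is not a detail left to a fuller document. Any saving after month 6 is outside the offset test while the full implementation cost is inside it.

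The size cannot be fixed from the documents. Under the curves tried, 33% to 100% of the 12-month saving is counted, with 50% for a constant effect lasting to month 12. The test is tilted against FLIP only if some saving continues after facilitation ends; otherwise nothing is lost. A reader might go further and call the offset result biased by a known factor of 2 to 3, but that requires both a sustained effect and savings that follow adherence, and the documents establish neither.

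The point concerns one secondary economic hypothesis and leaves the primary outcome untouched. It is worth correcting because the remedy is modest.

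**What to change.** 1. Extend the costing extract to month 12 after the start of the intervention, in both arms, with the same rules for admissions.
2. Report the difference-in-difference for cost, HLOS and ICU LOS separately for months 0-6 and 6-12.
3. Base the offset conclusion on 12-month hospital cost plus total FLIP cost. If the extract cannot be extended, say explicitly that the offset claim covers the delivery period only.
4. State the chosen window in the Cost analysis section, and correct the hospital-cost row or footnote b of Table 1 to match.

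A 12-month pre-period is optional, since concurrent controls already remove shared seasonal change.

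**Cost.** A larger extract at four hospitals from the costing databases that Table 1 already names, some added analysis, and an economic result about 6 months later, alongside the 12-month clinical result. No extra patients or audit days are needed. The documents do not describe the effort per extract, so this should be confirmed with the hospitals.
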